**4. Clinical trial design**

【Phase Ia】 Start at 0.1 mg/kg and dose escalation to 0.5 mg/kg and 1.0 mg/kg if tolerability is confirmed.

【Phase Ib】 Two dose escalation groups (0.1 mg/kg in case 0.5 mg/kg is MTD in phase Ia, 0.1 mg/kg in case 0.5 mg/kg is MTD in phase Ib) and a high-dose group in the tolerated dose group. Enrolment of 20 patients in each group.

【Criteria for tolerability】The dose one step below the MTD is the 'dose that has been found to be well tolerated'. The MTD is the dose at which the number of subjects who develop DLT during the period up to 28 days after the start of treatment with the study drug is 3 or more.

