**1-3-2. Overview of clinical trial data**

**1-3-2-1. Domestic phase I clinical study in patients with CCR4-positive relapsed ATL and Peripheral T-Cell Lymphoma (PTCL)**

In Japan, the Phase I study was conducted as a multicenter, open-label, dose-ranging study.

The subjects were ATL patients who relapsed or relapsed after CCR4-positive response to chemotherapy or PTCL patients including MF, etc. The safety and pharmacokinetics of intravenous administration of 0.01, 0.1, 0.5 or 1.0 mg/kg of mogamulizumab four times at weekly intervals were investigated. Efficacy was also examined as a secondary outcome. The dose at which dose-limiting toxicity (DLT) was observed in 3 subjects was defined as the maximum tolerated dose (MTD), the dose one level below the MTD was defined as the recommended dose (1.0 mg/kg if the MTD was not reached), and the recommended dose was determined by adding 3 subjects to the recommended dose. Three new patients were added to the recommended dose. In addition, subjects who relapsed or relapsed after achieving a response in the Phase I study were allowed to receive a second dose of mogamulizumab.

As no DLT was observed and MTD was not reached during the sequential dose increase from 0.01 mg/kg to 1.0 mg/kg (13 subjects in total), the recommended dose was set at 1.0 mg/kg and 3 more subjects were added (16 subjects in total). One of the three patients added to the recommended dose (1.0 mg/kg) had adverse events corresponding to DLT (neutropenia Grade 4, febrile neutropenia Grade 3, and skin rash Grade 3), but since DLT occurred in only one of six patients at the 1.0 mg/kg dose, the dose of 1.0 mg/kg Mogamulizumab was judged to be tolerable at doses up to 1.0 mg/kg.

As with other antibody drugs, mogamulizumab was associated with cytokine release syndrome/acute infusion reactions such as fever and chills, and decreased blood counts of lymphocytes, neutrophils, and leukocytes in a high frequency, all of which resolved spontaneously or with appropriate treatment such as drugs. Although thrombocytopenia was observed in about half of the subjects, all of them showed Grade 2 or lower decrease (Grade 1: 7 subjects, Grade 2: 1 subject), and all of them showed recovery. Serious adverse events that occurred in this study were herpes zoster, hypoxemia, and skin rash.

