[Phase Ib] The patient population will be divided into 20 patients in each group, each of whom will receive one dose and 0.1 mg/kg, the highest dose among the doses that were found to be well tolerated in Phase Ia (one step below the MTD or 1.0 mg/kg if the MTD has not been reached). The dose should be administered intravenously once a week for 8 consecutive weeks. However, if the dose of 0.1 mg/kg was the only dose that was found to be tolerated in Phase Ia, a dose of 0.1 mg/kg will be used in Phase Ib for 20 patients in each group.

<Rationale for Dose Setting>

If the safety and regulatory T-cell effects of Mogamulizumab in solid tumors are confirmed by this study, it is assumed that a drug that releases immunosuppression by a mechanism different from that of Mogamulizumab may be used in combination with Mogamulizumab in the future. In such a case, the possibility of autoimmune reactions would be higher than with single-agent administration of Mogamulizumab. Therefore, the low dose group was set at 0.1 mg/kg, the lowest dose established in Phase Ia, in order to obtain data over a wide dose range for confirming regulatory T-cell removal efficacy. The low-dose group was set at 0.1 mg/kg.

In the Phase Ib study, the high-dose group and the 0.1 mg/kg group were used in the Phase Ib study.

For subjects who showed SD or higher in the regulatory T-cell test, antigen-specific antibody immunoreactivity test, or diagnostic imaging after 8 doses, if the subject wished to receive maintenance dosing of the study drug and if the investigators determined that maintenance dosing of the study drug was appropriate, the investigator or other appropriate personnel would administer the study drug to the subject. If the subject wishes to receive maintenance dosing of the investigational drug and the investigator determines that maintenance dosing is appropriate, maintenance dosing of the investigational drug is allowed every 4 weeks after 12 weeks until the discontinuation criteria are met.

[figure not shown]
Phase Ia: Starting at 0.1 mg/kg, dose escalation to 0.5 mg/kg and 1.0 mg/kg if tolerability is confirmed.

Phase Ib: Among the treatment groups that were found to be well tolerated, a high-dose group and two 0.1 mg/kg groups (if 0.5 mg/kg was the MTD in Phase Ia, one 0.1 mg/kg group) were administered. Enrollment to be 20 patients in each group.

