**7-2. Group-to-group transition and procedures in phase Ia part**

The following procedure will be used to transition from the 0.1 mg/kg dose group to the 0.5 mg/kg dose group and then to the 1.0 mg/kg dose group. The Clinical Trial Coordinating Committee will decide on the transition of dosing groups. However, the efficacy and safety evaluation committee will also evaluate if necessary.

(1) If no DLT occurs in any of the 3 patients in the 0.1 mg/kg dose group, the patient will be shifted to the 0.5 mg/kg dose group.

If one of the three patients in the 0.1 mg/kg group develops DLT, three more patients will be enrolled in the 0.1 mg/kg group; if three or more patients in the 0.1 mg/kg group develop DLT, the MTD will be 0.1 mg/kg and the study will be terminated. If DLT occurs in 2 or less cases, the patient will be shifted to the 0.5 mg/kg group.

(2) If no DLT occurs in any of the 3 patients in the 0.5 mg/kg group, the patient will be moved to the 1.0 mg/kg group.

If 1 of 3 patients in the 0.5 mg/kg group develops DLT, enroll 3 more patients in the 0.5 mg/kg group. If more than 3 patients in the 0.5 mg/kg group develop DLT, the MTD will be 0.5 mg/kg and Phase Ia will be terminated. /Kg group if there are 2 or less cases of DLT.

(3) If none of the 3 patients in the 1.0 mg/kg group develop DLT, the MTD will be greater than 1.0 mg/kg and the Phase Ia portion will be terminated.

If 1 of 3 patients in the 1.0 mg/kg group develops DLT, enroll an additional 3 patients in the 1.0 mg/kg group; if 3 or more patients in the 1.0 mg/kg group develop DLT, the MTD will be 1.0 mg/kg and Phase Ia will be terminated. If DLT develops in 2 or fewer patients, the MTD will be 1.0 mg/kg. If fewer than 2 cases of DLT occur, the MTD will be greater than 1.0 mg/kg and Phase Ia will be terminated.

If the MTD is determined, investigational drug administration in the dose group corresponding to the MTD will be discontinued.

The safety evaluation for transfer to the next group (DLT observation period) can be determined based on information and test results up to 28 days after the start of the investigational drug administration, but the final safety evaluation period will be up to 24 weeks after the last dose in each case.

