**7-6. Expected number of cases to be enrolled**

**7-6-1. Phase Ia part**

0.1 mg/kg group 3 cases (maximum 6 cases)

0.5 mg/kg group 3 cases (maximum 6 cases)

1.0 mg/kg group 3 cases (max. 6 cases)

Total 9 cases (maximum 18 cases)

＜Rationale for setting the dose>

The dose was set up with reference to the usual Fibonacci's modification method in order to confirm safety up to 1.0 mg/kg, the dose for patients with ATL, while confirming that the dose limiting toxicity (DLT) does not exceed 2/6 (33.3%).

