**8-3. Definition of evaluation items**

**8-3-1. Definition of primary evaluation items**

1) Phase Ia

(1) Safety

The maximum tolerated dose (MTD) and dose-limiting toxicity (DLT) will be determined, and the type, frequency, and severity of adverse events will be observed. The Common Terminology Criteria for Adverse Events (CTCAE) v4.0 Japanese translation of the JCOG version^13)^ will be used for grading adverse events. Adverse events will be graded according to CTCAE v4.0.

The MTD is defined as the dose at which the number of subjects who developed DLT during the period up to 28 days after the start of treatment with the investigational drug was 3 or more. However, if the MTD is not reached at any dose, 1.0 mg/kg shall be the dose that was found to be well tolerated.

The observation period for DLT will be up to 28 days after the start of study drug administration. Among adverse events for which a causal relationship to the investigational drug cannot be ruled out, the following events will be considered DLTs.

Grade is determined according to CTCAE v4.0.

① Hematologic toxicity of Grade 4 or higher lasting for more than 7 days^*1^.

*1 "Febrile neutropenia" is defined as Grade 3 or higher regardless of duration, and "Neutropenia" is defined as treatment with G-CSF even if it is Grade 3 or lower. Lymphocytopenia" and "CD4 lymphocytopenia" are excluded.

② Non-hematologic toxicity of Grade 3 or higher

Symptoms judged to be "injection-related reactions" ("fever," "headache," "pain," "pruritus," "allergic reaction/hypersensitivity," etc.) are defined as Grade 4 or higher DLT. In addition, only AST (GOT), ALT (GPT), ALP, total bilirubin, creatinine, and potassium should be included in the clinical examination.

③ Others

i) Toxicity that caused the scheduled administration of the investigational drug to exceed 2 weeks beyond the specified scheduled administration date due to a Grade 3 in any of the symptoms judged to be "infusion-related reactions" in 2).

ii) Toxicities other than the above that prevented administration of the study drug more than twice during the DLT observation period due to the same event.

(2) Pharmacokinetics

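### The 1.0 mg/kg decision rule in section 7-2 gives 1/6 DLTs two opposite verdicts and calls 2/6 the MTD, although the MTD definition requires 3 or more

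*Protocol*

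**What the plan says.** Section 7-2 expands the 1.0 mg/kg cohort from three to six patients when one of the first three has a DLT. It then gives three statements in a row. The first makes 1.0 mg/kg the MTD at 3 or more DLTs. The other two begin "If DLT develops in 2 or fewer patients, the MTD will be 1.0 mg/kg. If fewer than 2 cases of DLT occur", and the last of them concludes that the MTD is greater than 1.0 mg/kg and that Phase Ia ends.

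Other parts of the protocol bear on the same count:

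- **Synopsis section 4:** the MTD is the dose at which the number of subjects with DLT "up to 28 days after the start of treatment with the study drug is 3 or more".
- **Section 8-3-1** (primary endpoint definition): the MTD is reached if the DLT count in the first 28 days of therapy "with the investigational drug was 3 or more. However, if the MTD is not reached at any dose, 1.0 mg/kg shall be the dose", meaning the tolerated dose.
- **Section 7-6-1:** the cohort size is justified by confirming that DLTs do not exceed 2 of 6 (33.3%).
- **Section 7-2, 0.1 mg/kg rule:** "If DLT occurs in 2 or less cases, the patient will be shifted to the 0.5 mg/kg group".
- **Section 1-3-2-1:** the earlier ATL/PTCL Phase I study judged 1.0 mg/kg tolerable "since DLT occurred in only one of six patients at the 1.0 mg/kg dose".

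Two provisions attach consequences to the verdict. Section 7-2 adds: "If the MTD is determined, investigational drug administration in the dose group corresponding to the MTD will be discontinued". Section 7-1 sets the Phase Ib high dose at "one step below the MTD or 1.0 mg/kg if the MTD has not been reached".

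**The concern.** Section 7-2 is the procedure for dose-group transition, which the coordinating committee decides, and MTD is a Phase Ia primary endpoint. At 1.0 mg/kg the procedure contradicts itself at 1/6 and contradicts the endpoint definition at 2/6. Taken together, its first two statements make 1.0 mg/kg the MTD whatever happens in the three added patients, so the expansion would decide nothing.

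If the committee follows the sentence on 2 or fewer DLTs, drug stops for patients still being treated at 1.0 mg/kg, and 0.5 mg/kg becomes the high dose for 20 Phase Ib patients. If it follows section 8-3-1, dosing continues and 1.0 mg/kg goes into Phase Ib. The recommended dose for Phase II, which section 8-3-2 bases on Phase Ib, is affected in turn.

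A lesser point of the same kind: the 0.5 mg/kg stopping rule in section 7-2 is worded as more than 3 DLTs. No action is stated at exactly 3/6, which the definition makes the MTD.

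**Working it through.** **Step 1. The plan's own figure.** Section 7-6-1 gives 2/6 as 33.3%; 2 ÷ 6 = 0.333. This agrees.

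**Step 2. Each possible total against each rule.** Expansion follows exactly one DLT in the first three patients, so the total among six is 1, 2, 3 or 4.

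| DLTs in six | 7-2: 3 or more | 7-2: 2 or fewer | 7-2: fewer than 2 | Definition (synopsis 4, 8-3-1) |
|---|---|---|---|---|
| 1 | – | MTD = 1.0 | MTD > 1.0 | MTD not reached |
| 2 | – | MTD = 1.0 | – | MTD not reached |
| 3 | MTD = 1.0 | – | – | MTD = 1.0 |
| 4 | MTD = 1.0 | – | – | MTD = 1.0 |

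Only 3/6 and 4/6 have one verdict that agrees with the definition. Deleting a single sentence does not repair the rule. Without the 2-or-fewer sentence, 2/6 has no verdict in section 7-2. Without the fewer-than-2 sentence, every expanded cohort is the MTD.

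**Step 3. How often these counts arise, given that 1.0 mg/kg is reached.** The protocol gives no expected DLT rate in solid tumours, so the true rate *p* is an assumption. Two values are worked through: 1/6, the rate seen at 1.0 mg/kg in the ATL/PTCL study, and 30%.

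- P(0 of 3) = (1 − p)³, which is 0.579 at p = 1/6 and 0.343 at p = 0.30.
- P(1 of 3) = 3p(1 − p)², which is 0.347 and 0.441.
- P(1/6) = P(1 of 3) × P(0 of 3): 0.347 × 0.579 = 0.201; 0.441 × 0.343 = 0.151.
- P(2/6) = P(1 of 3)²: 0.347² = 0.121; 0.441² = 0.194.
- Either count: 0.322 and 0.346 (summed before rounding).

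Over a wider range of assumed rates:

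| Assumed p | P(1/6) | P(2/6) | Either | Share of expanded cohorts |
|---|---|---|---|---|
| 10% | 0.177 | 0.059 | 0.236 | 97% |
| 1/6 | 0.201 | 0.121 | 0.322 | 93% |
| 20% | 0.197 | 0.147 | 0.344 | 90% |
| 30% | 0.151 | 0.194 | 0.346 | 78% |
| 33.3% | 0.132 | 0.198 | 0.329 | 74% |
| 40% | 0.093 | 0.187 | 0.280 | 65% |

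**Step 4. Not conditional on reaching 1.0 mg/kg.** The probability of passing one lower dose is P(0 of 3) + P(1 of 3) × P(at most 1 of 3). Two DLTs in the first three are counted as not escalating; this is an assumption, because section 7-2 gives no action for that result.

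- p = 1/6: 0.579 + 0.347 × 0.926 = 0.900. For two lower doses at the same rate, 0.900² = 0.810.
- p = 0.30: 0.343 + 0.441 × 0.784 = 0.689. For two doses, 0.474.
- Either count: 0.810 × 0.322 = 0.260 (0.261 with these rounded inputs); 0.474 × 0.346 = 0.164.
- 2/6 alone: 0.810 × 0.121 = 0.098; 0.474 × 0.194 = 0.092.

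These are the low ends, with the same DLT rate at all three doses. If 2/3 at the lower doses led to expansion instead, they would rise to 0.284 and 0.196 (either) and to 0.107 and 0.110 (2/6). The high ends assume no DLTs at 0.1 and 0.5 mg/kg and equal the conditional values in step 3.

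**The case against.** The strongest reply is that this is a translation fault and not a chosen rule. The English text elsewhere renders a sentence twice, sometimes wrongly the first time. Section 7-1, for instance, says blood levels in solid tumours would be lower than in ATL and then that they may be higher. On that reading the two sentences are one rule rendered twice, with the words for *greater than* lost the first time. The intended threshold can be recovered from synopsis section 4, section 8-3-1, section 7-6-1 and the 0.1 mg/kg rule. Hence 32–35% is the chance of meeting a disputed count, not of a wrong decision, and at 1/6 one of the two sentences does agree with the definition. With a low true rate the conflict is rarer: at 5%, 2/6 has probability 1.8% and either count 13.4%. Following the wrong sentence would also err towards a lower dose, and some of the first three patients might have finished their eight doses before the verdict.

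Much of this stands as a limit on size. The translation origin is plausible but cannot be confirmed, since the original is not shown. The probabilities do describe counts, and 2/6 is the clearer conflict because no sentence in the 1.0 mg/kg rule agrees with the definition there. The dosing stop would affect only patients still on drug.

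It does not remove the fault. The sentences are current operative text, and nothing in the protocol says that section 8-3-1 overrides section 7-2. Even if the first sentence is discarded as a duplicate, the surviving one says fewer than 2, which still leaves 2/6 undecided. The 0.5 mg/kg wording sits beside visibly damaged text and is most likely meant as 3 or more; it carries little weight alone.

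**Conclusion.** The rule is wrong as written. In an expanded 1.0 mg/kg cohort, 1/6 has two opposite verdicts within section 7-2, and 2/6 is declared the MTD against the definition of a primary endpoint. The sentence on 2 or fewer DLTs is the outlier against the rest of the protocol.

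Given that 1.0 mg/kg is reached, one of the two counts arises with probability 32% (p = 1/6) or 35% (p = 30%), and 24–35% across the assumed rates of 10% to 40%. The count 2/6 alone has probability 12% or 19%. Not conditional on reaching that dose, the ranges are 26–32% and 16–35% for either count, and 10–12% and 9–19% for 2/6. All of these rest on assumed true DLT rates and independent patients. The contradiction itself rests on the text alone and does not depend on them.

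**What to change.** In section 7-2 at 1.0 mg/kg, replace the two sentences that follow the 3-or-more rule with one: *with 2 or fewer DLTs among the six patients, the MTD is greater than 1.0 mg/kg and Phase Ia ends.* At 0.5 mg/kg, change the stopping count from more than 3 to 3 or more. Every total in an expanded cohort then has one verdict: 1/6 and 2/6 tolerated, 3/6 and 4/6 the MTD. This agrees with synopsis section 4, sections 8-3-1 and 7-6-1, and the 0.1 mg/kg rule.

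The cost is a protocol wording change of two sentences and one phrase. It needs no extra patients. Checking the original-language text at the same time would show whether the fault lies only in the translation.

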**7-3. Transition to phase Ib part**

After completion of the DLT observation period of Phase Ia, Phase Ib should be conducted in the higher tolerated dose group and the 0.1 mg/kg dose group. The Clinical Trial Coordinating Committee will decide whether to proceed to Phase Ib. However, the efficacy and safety evaluation committee will also evaluate if necessary.

**7-4. Planned duration of the clinical trial**

February 2013 - March 2016

**7-5. Method of enrolment and allocation**

**7-5-1. Procedure for enrolment of subjects**

After receiving approval from the Clinical Trial Review Committee and submitting the clinical trial plan, the investigators at each site obtain consent in writing after providing sufficient explanation to the candidate cases, conduct necessary tests to determine eligibility, and request case registration to the Case Registration Center. The case registration center will determine the eligibility of the cases, assign a designated registration number only to subjects who are determined to be eligible, and report the results to the principal investigator, etc. via fax.

**7-5-2. Allocation**

The registration center allocates the prescribed doses to subjects in Phase Ia according to "7-2. In addition, when Phase Ib is conducted with two dose groups, the registration center will dynamically perform random allocation using the minimization method with carcinoma as the allocation factor so that there is no large difference in the number of subjects in the two groups within a carcinoma.

**7-6. Expected number of cases to be enrolled**

**7-6-1. Phase Ia part**

0.1 mg/kg group 3 cases (maximum 6 cases)

0.5 mg/kg group 3 cases (maximum 6 cases)

1.0 mg/kg group 3 cases (max. 6 cases)

Total 9 cases (maximum 18 cases)

＜Rationale for setting the dose>

The dose was set up with reference to the usual Fibonacci's modification method in order to confirm safety up to 1.0 mg/kg, the dose for patients with ATL, while confirming that the dose limiting toxicity (DLT) does not exceed 2/6 (33.3%).

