Overall Survival (OS) is defined as the period from the start date of study drug administration to death from any cause. For patients who survived without confirmed death, the date of last confirmed survival shall be considered as the date of last confirmation of survival, and for patients who were lost to follow-up, the date of last confirmed survival shall be considered as the date of discontinuation.

2) Phase Ib

(1) Tumor reduction effect

See "8-3-2. Definition of Secondary Endpoints 1) Phase Ia".

(2) Progression-free survival

See "8-3-2. Definition of Secondary Endpoints 1) Phase Ia".

(3) Overall survival

See "8-3-2. Definition of Secondary Endpoints 1) Phase Ia".

(4) Determination of recommended doses for Phase II and beyond

Recommended doses for Phase II and beyond will be determined based on a comprehensive review of the safety and efficacy in eliminating regulatory T cells in Phase Ib.

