**11-4. Analysis items and methods**

Detailed analysis methods are described in the "Statistical Analysis Plan" and "Pharmacokinetic Analysis Plan" to be prepared separately.

1) Safety

(1) Number of DLT cases

The number of DLTs and the incidence rate of DLTs per treatment group in Phase Ia are shown.

(2) Occurrence of adverse events and adverse reactions

Adverse events that occurred in Phase Ia and Phase Ib are summarized in the table. All adverse events and adverse drug reactions are summarized by the MedDRA basic terms and by major organ category, and the number and percentage of adverse events for each treatment group are shown.

(3) Gene analysis

Exploratory studies will be conducted as necessary.

2) Efficacy

(1) Efficacy in eliminating regulatory T cells

Summary statistics are calculated for each treatment group.

(2) Antigen-specific antibody immune response

To be investigated in an exploratory manner for each treatment group.

(3) Anti-tumor effect

The number of responders and the percentage of responders (response rate) will be calculated for each treatment group.

(4) Progression-free survival (PFS)

Progression-free survival is calculated using the Kaplan-Meier method.

(5) Overall survival (OS)

Overall survival is calculated using the Kaplan-Meier method.

(6) Immunostimulatory effect

To be examined on an exploratory basis as necessary.

(7) Gene analysis

To be explored as necessary.

In addition, the relationship between regulatory T-cell elimination effect and anti-tumor effect, antigen-specific antibody immune response, etc. will be explored.

3) Pharmacokinetics

(1) Plasma Mogamulizumab concentration

Plasma concentrations of Mogamulizumab will be listed and descriptive statistics for each dose will be shown; plasma concentration trends of Mogamulizumab will be plotted graphically as individual subject data and mean (+ standard deviation) versus blood collection time on a real and log scale.

(2) Mogamulizumab pharmacokinetic parameters

Calculate the pharmacokinetic parameters for each subject as indicated in "8-3-1 Definition of primary endpoints 1) Phase Ia Part (2) Pharmacokinetics" and calculate descriptive statistics for each dose.

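### Protocol 7-6-1 presents 2/6 (33.3%) as something Phase Ia confirms; it holds only as an observed-count threshold, and DLT counting stops before the larger Phase Ib groups that could inform the true rate

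*Protocol*

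**What the plan says.** Section 7-6-1 plans three patients per dose at three doses, expandable to six ("Total 9 cases (maximum 18 cases"). Its rationale is to check safety up to the 1.0 mg/kg dose used in ATL, "while confirming that the dose limiting toxicity (DLT) does not exceed 2/6 (33.3"%).

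Section 7-2 gives the escalation rule:
- "If no DLT occurs in any of the 3 patients in the 0.1 mg/kg dose group", escalation proceeds.
- "If one of the three patients in the 0.1 mg/kg group develops DLT, three more patients will be enrolled in the 0.1 mg/kg group".
- "If DLT occurs in 2 or less cases, the patient will be shifted to the 0.5 mg/kg group".
- At the top dose, "If none of the 3 patients in the 1.0 mg/kg group develop DLT, the MTD will be greater than 1.0 mg/kg".

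The MTD, in section 4 of the Summary and in 8-3-1, is the dose at which three or more subjects have a DLT within 28 days of starting treatment.

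Section 11-4 1)(1) states the DLT analysis: "The number of DLTs and the incidence rate of DLTs per treatment group in Phase Ia are shown". For Phase Ib, 8-3-1 asks for the type, frequency and severity of adverse events under CTCAE v4.0 and has no DLT count. Section 8-3-2 2)(4) then says: "Recommended doses for Phase II and beyond will be determined based on a comprehensive review of the safety" and of regulatory T-cell elimination in Phase Ib.

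**The concern.** The 7-6-1 sentence is the only rationale for the Phase Ia sample size, and MTD and DLT are primary endpoints of that part. It turns a count into a percentage and links it to confirming safety, so a reader can take it as a statement about the underlying DLT rate. Three to six patients cannot support such a statement.

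The tolerated dose fixes the high-dose arm of Phase Ib and feeds the Phase II recommendation. If 2/6 is read as an established rate, the dose goes forward with more assurance than the data give. Phase Ib then treats 20 patients per group, but the DLT measure used to call the dose tolerated is not carried into it. The dose review would have adverse-event tables but no DLT rate on the same 28-day definition from most of the patients treated at that dose.

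**Working it through.** **The protocol's own figures.** 2/6 = 33.3%, the largest count below the MTD trigger of three. 3 × 3 = 9 and 3 × 6 = 18. All reproduce. The protocol states no target true rate, error limit or confidence level, so there is no sample-size formula to reproduce.

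**Chance that one dose passes.** Let p be the true DLT probability, with independent patients.

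Reading A (2/3 stops): P = P(0 of 3) + P(1 of 3) × P(at most 1 of the next 3).
- p = 1/3: 0.2963 + 0.4444 × 0.7407 = 0.626
- p = 0.5: 0.125 + 0.375 × 0.5 = 0.313

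Reading B (2/3 also expands to six): add P(2 of 3) × P(0 of the next 3).
- p = 1/3: 0.6255 + 0.2222 × 0.2963 = 0.691
- p = 0.5: 0.3125 + 0.375 × 0.125 = 0.359

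Reading C (1.0 mg/kg, the sentence requiring fewer than two DLTs): P(0 of 3) + P(1 of 3) × P(0 of the next 3).
- p = 1/3: 0.2963 + 0.4444 × 0.2963 = 0.428
- p = 0.5: 0.125 + 0.375 × 0.125 = 0.172

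| True DLT rate | A | B | C |
|---|---|---|---|
| 33.3% | 62.6% | 69.1% | 42.8% |
| 40% | 49.6% | 55.8% | 30.9% |
| 50% | 31.3% | 35.9% | 17.2% |
| 60% | 16.5% | 19.3% | 8.2% |

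**What a passing result excludes.** These are exact (Clopper-Pearson) one-sided upper limits, taking n as fixed. With no events the 95% limit is 1 − 0.05^(1/n), so 0/3 gives 1 − 0.05^(1/3) = 63.2%.

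| Passing result | 95% limit | 90% limit | 80% limit |
|---|---|---|---|
| 0/3 | 63.2% | 53.6% | 41.5% |
| 1/6 | 58.2% | 51.0% | 42.2% |
| 2/6 | 72.9% | 66.7% | 58.5% |

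None is below 33.3%. The highest confidence that the rate is below one third, from any passing result at one dose, is 1 − (2/3)³ = 70.4%, from 0/3. Even 0/6, which the rule does not produce, has a 95% limit of 39.3%.

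**Borrowing across doses.** If DLT risk does not fall with dose, 0/3 at all three levels gives 0/9 for 0.1 mg/kg, with a 95% limit of 28.3%. The limit is 39.3% (0/6) for 0.5 mg/kg and stays at 63.2% for 1.0 mg/kg.

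**What Phase Ib could add.** The 95% limits are 13.9% for 0/20, 21.6% for 1/20, 28.3% for 2/20 and 34.4% for 3/20. With Phase Ia added (20 + 3 = 23 or 20 + 6 = 26 patients), they are 30.4% for 3/23 and 31.8% for 4/26. So up to 2/20, 3/23 or 4/26 would exclude 33.3%. The chance of at most 2/20 is 92.5%, 67.7% and 20.6% at true rates of 5%, 10% and 20%, and 1.8% at 33.3%.

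**Are the Phase Ib data there?** The protocol records blood counts at each dose (9-5-4), concomitant treatment (9-3), onset and worst dates (10-2-2), grade (10-2-3), action on study drug (10-2-5) and causality (10-2-8). These are the inputs to the 8-3-1 definition.

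**Wording in 7-2 that drives the range.**
- Exactly 2/3 has no stated action at any dose.
- At 0.5 mg/kg the MTD trigger is written as more than three, against three or more in the definition.
- At 1.0 mg/kg, one sentence makes two or fewer DLTs an MTD of 1.0 mg/kg. The next makes fewer than two an MTD above it. These overlap for 0 and 1, and the first conflicts with the definition.

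**The case against.** The strongest reply is that the text gives a count out of six, and this matches the rule: a dose passes with at most two DLTs and reaches the MTD at three. Every passing dose meets that ceiling by construction. This stands. A reader might infer that no Phase Ia result could ever satisfy the sentence, but that follows only if 33.3% means the true rate, which the protocol does not say. On the count reading, however, the confirmation follows automatically from passing and says nothing further about safety.

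A reader might also infer that the trial report must declare a true rate of 33.3% or less. No section requires this: 7-6-1 is a sample-size rationale, and 8-3-1 and 11-4 call for the MTD, DLT counts and rates, and adverse events. Nor does the design breach an error limit of its own, because it states none.

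Phase Ib safety is not ignored. Adverse events are a primary endpoint, are tabulated by group and enter the dose review. What is missing is a DLT rate on the Phase Ia definition. Phase Ib was sized for the regulatory T-cell effect and feasibility, so a DLT table there is an improvement that the protocol did not promise.

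Exact intervals are ordinary SAP content, and 11-4 defers detailed methods to an SAP that is not shown, so their absence is no fault. The 7-6-1 wording and the Phase Ia-only scope in 11-4 are protocol statements. Finally, small samples are a feature of any 3-to-6-patient escalation rule. That is so, and the rule itself is not in dispute here.

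**Conclusion.** The point holds in a limited form. As an observed threshold, 2/6 is consistent with the MTD definition. As a statement about the true DLT rate at a given dose it is unsupported: passing results leave 95% upper limits of 58% to 73%. A dose at 33.3% passes 63-69% of the time and one at 50% passes 31-36%, or 43% and 17% under the conflicting 1.0 mg/kg sentence.

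These figures assume independent patients, fixed-n exact limits and a 95% level chosen here; the 90% and 80% levels give the same conclusion. The statement is per dose: under a non-decreasing dose-toxicity assumption, 0/9 would exclude 33.3% for 0.1 mg/kg, but the limit for 1.0 mg/kg would not change.

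Confining the DLT tabulation to Phase Ia leaves the estimate at a candidate Phase II dose on 3 to 6 patients when about 23 to 26 could contribute. Even then, excluding 33.3% is not assured: at a true rate of 10%, Phase Ib alone would do so about 68% of the time. The change is worth making because it costs little. The rewording of 7-6-1 is its firmest part.

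**What to change.** 1. In 7-6-1, describe 2/6 as the observed count at which the decision turns. State that it does not show the true rate to be 33.3% or less, and give the pass probabilities as a range.
2. In 11-4 1)(1), also tabulate events that meet the 8-3-1 DLT definition in the first 28 days of Phase Ib, per dose and with exact limits. Show Phase Ib alone as the primary figure, with Phase Ia added beside it. State the denominator, because 7-2 adds patients when too few doses could be given for reasons other than DLT. Name this table as an input to the dose review in 8-3-2 2)(4).
3. Reconcile the 7-2 sentences (2/3 unaddressed; the differing triggers at 0.5 and 1.0 mg/kg) with the MTD definition in section 4 of the Summary and in 8-3-1. Which wording applies is for the sponsor to settle.

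The cost is protocol wording and one extra table from data already collected. The tolerability statement becomes less favourable. The pooled rate is slightly optimistic, because Phase Ia doses go forward only after few DLTs, which is why Phase Ib alone comes first. Items 1 and 2 leave the doses, escalation rule and sample size as they are.
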